## Abstract

**Background:**

Postoperative gastrointestinal dysfunction (PGID) is a common complication arising from colorectal cancer surgery. Attributing factors, such as anesthesia, surgical retraction, and early intake of water, can inhibit gastrointestinal motility, causing constipation, reduction or absence of bowel sounds, nausea, vomiting, and other symptoms. Delayed recovery in gastrointestinal function can lead to intestinal obstructions or paralysis, anastomotic leaks, and other complications, affecting the patient’s recovery and quality of life negatively. Due to its complex pathophysiology, treatment for PGID in colorectal patients has remained a challenge. Acupuncture is an alternative therapy commonly used for postoperative recovery. This study aims to evaluate the therapeutic efficacy and safety of acupuncture on PGID. Through the complementation of acupuncture and enhanced recovery after surgery (ERAS) protocols, the advantages of acupuncture treatments could be demonstrated to promote its application in future clinical practice.

**Methods:**

The study design is a prospective randomized controlled trial (RCT). One hundred sixty postoperative colorectal cancer patients will be recruited from Cancer Hospital Chinese Academy of Medical Sciences (CICAMS). Subjects who fulfill inclusion criteria will be randomly assigned into the acupuncture group (AG) (*n* = 80) or control group (CG) (*n* = 80). AG will receive acupuncture treatment and perioperative care guided by ERAS protocols, and CG will only receive perioperative care guided by ERAS protocols. The intervention will begin on the first day post-surgery, continuing for 4 days, with a follow-up assessment in a month. Time of first postoperative flatus would be the primary outcome measure. Secondary outcome measures include the time of first postoperative defecation, time of first fluid intake, time of first ambulation, postoperative hospital stay, gastrointestinal reaction score, acupuncture sensation evaluation scale, laboratory tests, postoperative quality of life, readmission rate, and postoperative complications. All results are evaluated from baseline, post-treatment, and upon follow-up.

**Discussion:**

The results of the study would help elucidate evidence of the therapeutic effects of acupuncture on the recovery of postoperative gastrointestinal function. The objective of the study aims for the eventual inclusion of acupuncture in the ERAS protocol, allowing for wider application in clinical practice.

**Trial registration:**

ClinicalTrials.gov ChiCTR2000036351. Registered on August 22, 2020

## Administrative information

Note: the numbers in curly brackets in this protocol refer to SPIRIT checklist item numbers. The order of the items has been modified to group similar items (see http://www.equator-network.org/reporting-guidelines/spirit-2013-statement-defining-standard-protocol-items-for-clinical-trials/).

## Introduction

### Background and rationale {6a}

Colorectal cancer is a common malignant condition involving the gastrointestinal tract. With the aging population and changes in diet structures, incidence and mortality rates of colorectal cancer have seen a rising trend through the years [1]. Epidemiological studies have shown [2, 3] that in 2016, newly diagnosed cases and deaths of colorectal cancer in the USA were 135,000 and 50,000, respectively, and China has a higher ratio of newly diagnosed cases to death (50.8%) when compared with the USA (37%). In China, the incidence of colorectal cancer in males and females ranked 4th and 3rd, respectively, while mortality rates ranked 5th and 4th, respectively. The incidence of colorectal cancer for the age group below 50 has also shown an increasing trend. Surgical intervention remains the main treatment for colorectal cancer, despite surgical trauma and postoperative complications. Postoperative gastrointestinal dysfunction (PGID) is one of the most common complications and is often associated with administration of anesthesia, surgical retraction, postoperative fasting, usage of analgesics, prolonged bed rest, etc. [4, 5], and include symptoms such as distention and absence of flatus or bowel, accompanied by varying degrees of nausea, vomiting, and fever, leading to longer recovery periods, decrease in quality of life, and increase consumption of medical resources [6]. Current methods to promote recovery of gastrointestinal function include postoperative conventional treatments and prokinetic drugs such as domperidone and cisapride. However, the therapeutic efficacy of these drugs is less than ideal and accompanied with various side effects, possibly due to over-stimulation of gastrointestinal motility that could affect postoperative recovery negatively [7].

Enhanced recovery after surgery (ERAS) is an evidence-based approach that employs a series of multimodal and optimized perioperation measures to reduce surgical trauma and stress response, promote physiological and psychological well-being, and facilitate faster recovery [8]. As a newly implemented perioperative management principle, specific measures include preoperative education and counseling, selective preoperative bowel preparation, selective preoperative sedation, 30–60-min preoperative antibiotic prophylaxis, standardized anesthetic protocol, perioperative fluid intake management, prevention of intraoperative hypothermal, early removal of urinary catheters, multimodal postoperative analgesia, early postoperative food intake, early mobilization, etc. [9]. ERAS protocol has the advantages of faster recovery, lesser complications, shorter hospitalization, and lower medical cost and is widely adopted and implemented in various surgical fields [10]. With rapid developments in the field of surgical rehabilitation, measures to improve postoperative recovery in colorectal cancer patients are gradually being optimized. At present, although ERAS has lowered the incidence of postoperative complications, a portion of patients, in particular elderly, diabetic patients, or individuals who have poor digestive functions, could still develop long-term, refractory, recurrent complications [11].

Acupuncture is a unique and natural treatment method originating from China, and the practice of which to treat digestive ailments had been recorded over a few thousand years [12]. Recent evidence shows that [13, 14] acupuncture exhibits higher effectiveness over western medications, displaying various advantages such as expediting the recovery of gastrointestinal function, reducing postoperative complications, boosting immunity, and improving quality of life, when applied as a complementary treatment for colorectal cancer. Additionally, acupuncture possesses qualities of a safe and economical treatment and holds an irreplaceable role in rehabilitation medicine [15]. However, existing studies have their limitations, including small study samples, poorly designed experiments, low credibility of experimental results, etc. Our study aims to further investigate the therapeutic efficacy of acupuncture on postoperative recovery of gastrointestinal functions, by comparing trial results through complementation of acupuncture and ERAS protocol-guided laparoscopic radical resection of colon cancer versus solely ERAS protocol-guided laparoscopic radical resection of colon cancer, to provide statistical evidence for the inclusion of acupuncture in the ERAS protocols for colorectal cancer.

### Objectives {7}

To determine the therapeutic efficacy of acupuncture on the recovery of postoperative gastrointestinal function in colorectal cancer patientsTo provide statistical evidence for the inclusion of acupuncture into ERAS protocols

### Trial design {8}

The study is a single-center, prospective, parallel, randomized controlled clinical trial. Subjects who fulfill inclusion criteria and signed the informed consent form will be randomly assigned to either the acupuncture group (AG) or control group (CG) in a 1:1 ratio. Assessments are made prior to treatments and on the 4th day and 1 month after the treatments (Fig. 1).

**Fig. 1 Fig1:**
[figure not shown]
Flowchart of the study design

The purpose of this study is to design a high-quality randomized controlled trial and realize the complete randomization of participants, and the evaluators and data analysts are blinded, so as to provide reliable data for the recovery of gastrointestinal function of colorectal cancer after acupuncture treatment. However, the framework of this trial is not perfect. First, this study failed to establish false acupuncture, and the comforting effect of acupuncture cannot be ruled out. Second, the included cases are completely random without too many restrictions, but the clinical situation of patients is complex, and the tumor stage, operation mode, and TCM syndrome type may be related to the speed of postoperative gastrointestinal function recovery. It is better to carry out stratified observation. Third, both patients received perioperative care guided by eras, which achieved the ceiling effect, and the acupuncture effect may not be obvious. Fourth, the patients knew the grouping situation and were not blinded.

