#### Secondary outcomes

Secondary outcomes include the time of first postoperative defecation, time of first fluid intake, and time of first ambulation, which are obtained through the assistance of family members and caregivers, via inquiry and records of patient’s status. Other secondary outcome measures such as gastrointestinal reaction score (postoperative pains, distention, nausea, vomiting), acupuncture sensation evaluation scale, laboratory test, postoperative hospital stay, quality of life, readmission rate, and other postoperative complications (fever, pneumonia, wound infection, bleeding, etc.) are assessed and evaluated by our investigators. The first postoperative evaluation of all patients was performed 12–24 h after operation to ensure that the patients were awake.

For gastrointestinal reaction score, postoperative pain will be evaluated regularly at three times a day using the visual analog scale (VAS), and the three scores will be averaged and tabulated with dosage and frequency of patient-controlled analgesia (PCA) and analgesic medication used. The extent of distention is recorded using the Likert scale [17], postoperatively from day 1 to 4. The extent of nausea is recorded using the VAS, postoperative from day 1 to 4. Vomiting will be counted daily.

For Acupuncture Sensation Evaluation Scale, acupuncture sensations are assessed after every acupuncture treatment session through inquiring about patient’s sensations.

For laboratory test, venous blood will also be collected on the day prior to operation, as well as the first and third day after the laparoscopy, to assess the safety of acupuncture base on blood examinations and biochemical indicators.

Postoperative hospital stay is measured from the day of the laparoscopy procedure till the day of discharge.

Quality of life is assessed through the Quality of Life Questionnaire (QLQ-c30), provided to patients prior to operation and 1 month after the operation [18].

For readmission rate, evaluate the readmission of patients 1 month after the operation, record the reasons for readmission in detail, and finally calculate and analyze.

Adverse events include postoperative complications and adverse acupuncture events. Postoperative complications are recorded and evaluated using the Clavien Dindo Classification [19]. Adverse acupuncture events including subcutaneous hematoma, continuous acupuncture afterfeeling, and needle stagnation will be recorded by the assessor.

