### Sample size {14}

Our study estimates that a mean decrease of 8 h in time of first flatus after application of acupuncture to promote recovery in postoperative gastrointestinal functions is of significant value. The literature review showed the standard deviation of time of first flatus between the study group and control group to be 12.28 and 14.57, respectively. Using a unilateral test of superiority, PASS.11 software is used to compute sample size. Using *α* = 0.05, *β* = 0.1, and power = 0.9, 68 subjects are required in each group, with a total of 136 subjects needed for the study. Estimating a 20% dropout rate, a minimum recruitment of 160 subjects is required.

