### Statistical methods

#### Statistical methods for primary and secondary outcomes {20a}

Spss22.0 software was used to analyze and process the clinical observation data, in which in the descriptive statistical analysis, qualitative indicators were described by frequency table and percentage and quantitative indicators were described by mean and standard deviation. Comparison of the two groups was performed: quantitative data in line with normal distribution using the *t* test, homogeneity test of variance between groups, with 0.05 as the test level, uneven variance using Satterthwaite method for correction of *t* test, and not in line with normal distribution using Wilcoxon rank-sum test. The hypothesis test uses a two-sided test and gives the test statistics and the corresponding *p* value, with *p* ≤ 0.05 as statistically significant. All (S)AE(I)s will be summarized and recorded including the nature, date and time of onset, date of resolution, determination of seriousness, severity, action taken, outcome, and possible causality to study treatment. SAE data will be presented in a descriptive manner.

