Patients between ages 18 and 80 have been included in the study to cover a larger spectrum of the demographics. At the same time, patients after colorectal cancer surgery were completely randomized, and the outcome evaluators and statisticians were blinded, and the reliability of the trials was high. In addition, assessment of gastrointestinal function-related clinical parameters and laboratory tests is done to aid in the evaluation of the efficacy and safety of acupuncture treatments, ultimately providing the basis for the overall evaluation of the effects of acupuncture on recovery of gastrointestinal function from colorectal cancer operations. Clinical parameters for gastrointestinal function include the time of first postoperative flatus, time of first postoperative defecation, time of first fluid intake, hospitalization period, etc. Importantly, laboratory tests such as blood test and biochemical indicators have been included in our study to assess the safety of acupuncture. One of the advantages of our study is the conduct of a follow-up to gather response through the QLQ-c30 to assess patients’ quality of life 1 month after the operation, which will reflect the long-term impact of acupuncture on postoperative colorectal patients.

However, there are limitations to the study. Firstly, ensuring punctual and accurate follow-ups is both an important and difficult task, and insertion of rectal tubes in a portion of our study subjects might cause inaccuracies in reporting the time of first postoperative flatus by the patients. Secondly, the study lacks a sham acupuncture control group, due to difficulties in blinding of study subjects. Lastly, both groups received perioperative nursing guided by ERAS protocol, so the role of acupuncture may be ignored. Despite these limitations, the study should elucidate the general effect of acupuncture on postoperative recovery.

In conclusion, we hope that through rigorous clinical study, statistical evidence of acupuncture in promoting recovery of gastrointestinal function in post-laparoscopy colorectal cancer patients can be demonstrated, providing the basis for the inclusion of acupuncture into ERAS principles and protocols, to encourage the application of acupuncture in the aforementioned condition after conventional surgical procedures.

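### The protocol fixes unadjusted two-sample tests although it names possible prognostic factors and collects a preoperative QLQ-C30; the cost is precision, not validity

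*Protocol article*

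**What the plan says.** **Prognostic factors.** The text under Fig. 1 in Trial design {8} lists the study's limitations. It describes allocation as completely random, states that "the tumor stage, operation mode, and TCM syndrome type may be related to the speed of postoperative gastrointestinal function recovery", and adds that a stratified approach would be better. Sequence generation {16a}, Concealment mechanism {16b} and Implementation {16c} name no stratification factor.

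**Rectal tubes.** The Discussion says that "insertion of rectal tubes in a portion of our study subjects might cause inaccuracies in reporting the time of first postoperative flatus". It gives no time of insertion.

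**Baseline quality of life.** Under Secondary outcomes, the QLQ-C30 is "provided to patients prior to operation and 1 month after the operation". Blood is drawn the day before surgery and on postoperative days 1 and 3.

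**Analysis.** Statistical methods {20a} sets the group comparison as "quantitative data in line with normal distribution using the" t test, with a Satterthwaite correction for unequal variances and the Wilcoxon rank-sum test where normality fails. None of these carries a covariate. The same section says "The hypothesis test uses a two-sided test and gives the test statistics and the corresponding" p value. Section {20b} plans no subgroup analyses. Section {20c} remarks that mixed models need no imputation, but no mixed model, outcome or covariate is defined anywhere.

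**The concern.** The protocol identifies variables that may drive its primary outcome, says that stratification would have been better, and then specifies an analysis that uses none of them. It also measures quality of life before surgery without saying how that score enters the 1-month comparison. This is a choice of test made in the document, not merely a detail left open.

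If the named factors are prognostic, an unadjusted comparison gives wider confidence intervals than the data allow. A chance imbalance in the trial as realised then stays in the reported difference. For QLQ-C30, whose 1-month follow-up the Discussion counts among the study's advantages, the preoperative score is an obvious covariate, and leaving it out can be expensive.

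**Working it through.** **1. The plan's own figure.** Sample size {14} targets "a mean decrease of 8 h in time of first flatus", with SDs of 12.28 and 14.57, α = 0.05 and β = "0.1, and power = 0.9, 68 subjects are required in each group, with a total of 136 subjects needed for the study". It says: "Using a unilateral test of superiority, PASS.11 software is used to compute sample size".

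- Mean variance: (12.28² + 14.57²)/2 = (150.8 + 212.3)/2 = 181.5 h², so SD = 13.47 h.
- n per group = 2 × 181.5 × (z_α + z_β)²/8².
- One-sided, as stated: 2 × 181.5 × (1.645 + 1.282)²/64 ≈ 48.6, so 49 (50 with the t distribution).
- Two-sided: 2 × 181.5 × (1.960 + 1.282)²/64 ≈ 59.6, so 60 (61 with t).

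The stated 68 is not reproduced either way. That is a separate matter. Here it means only that the unadjusted two-sided test has some power in reserve.

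**2. Effect of adjustment on the primary outcome.** With 80 per arm and the stated 20% dropout, 80 × 0.8 = 64 remain. Adjustment for covariates that explain a share R² of the variance multiplies the SD by √(1 − R²). The noncentrality is 8/(13.47 × √(1 − R²) × √(2/n)), two-sided α = 0.05, noncentral t. R² is not in the documents, so a range is shown.

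| R² (assumed) | SE factor √(1 − R²) | Power, 64 per arm | Power, 68 per arm | n per arm for 90% (normal) |
|---|---|---|---|---|
| 0 | 1.00 | 91.5% | 93.0% | 60 |
| 0.10 | 0.95 | 94.0% | 95.2% | 54 |
| 0.20 | 0.89 | 96.1% | 97.0% | 48 |
| 0.30 | 0.84 | 97.9% | 98.4% | 42 |

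Confidence intervals would be about 5% narrower at R² = 0.10 and about 16% narrower at 0.30.

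**3. Chance imbalance.** Take a binary factor present in 40% of patients (assumed), with 80 per arm. The SD of the difference in prevalence is √(2 × 0.4 × 0.6/80) = 7.7 percentage points, so a difference of 10 points or more has a probability of about 20%. If the factor shifts flatus time by 12 h (assumed), such an imbalance moves the realised difference by 0.10 × 12 = 1.2 h. The standard error at 80 per arm is 13.47 × √(2/80) = 2.13 h, so the shift is 1.2/2.13 = 0.56 SE, and the standard error already allows for it.

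The protocol's SDs limit how strong such a factor can be:

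- 12 h: 0.4 × 0.6 × 12² = 34.6 h², or 19% of 181.5 h².
- 24 h: 0.4 × 0.6 × 24² = 138 h², or 76% of 181.5 h², which is implausible for one factor.

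**4. QLQ-C30.** Let r be the correlation between the preoperative and 1-month scores (not in the documents), with equal variance at the two times. Relative to an unadjusted comparison of 1-month scores, the variance is 1 − r² for ANCOVA and 2(1 − r) for change scores.

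| r (assumed) | ANCOVA, 1 − r² | Change score, 2(1 − r) |
|---|---|---|
| 0.3 | 0.91 | 1.40 |
| 0.5 | 0.75 | 1.00 |
| 0.7 | 0.51 | 0.60 |

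ANCOVA saves 9%, 25% and 51% against the bare 1-month score. It also has the smaller variance against the change score in every row.

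**The case against.** **The analysis plan is not shown, and this is a condensed article.** Covariate lists are commonly left to that plan, and their absence alone would be no finding. That is accepted. Section {20a}, however, names the tests for quantitative outcomes, and none of them can take a covariate.

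**Baseline QLQ-C30 may be used after all.** The abstract says in general terms that results are evaluated from baseline onwards, section {20a} does not say whether the test is applied to 1-month or change scores, and section {20c} mentions mixed models. So it is too much to say that the baseline is deliberately discarded. What stands is that no stated comparison says how it enters, and a change score would still be less efficient than ANCOVA.

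**Power is already adequate.** Correct: 91.5% at 64 per arm exceeds the planned 90%. The gain in power is modest.

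**Operation mode is already narrowed.** Only laparoscopic radical resection is eligible, and conversions to open surgery are excluded. This limits what adjustment can gain but does not remove differences in operation type and tumour site.

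**Stronger readings that the documents do not support.**

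- A reader might infer that the factors are strongly prognostic. The protocol says only that they may be related, and gives no effect size.
- A reader might infer that chance imbalance biases the result. Under randomisation the unadjusted estimator is unbiased and the test valid.
- A reader might infer that rectal-tube use should be adjusted for, or tube patients excluded. The Discussion describes possible misreporting of the outcome in a subset. A yes/no covariate does not correct a misreported time. Because the time of insertion is not given, conditioning on the tube could mean conditioning on a post-randomisation variable.

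**Conclusion.** The point holds as one of efficiency. The protocol fixes unadjusted tests for all quantitative outcomes while naming possible prognostic factors and collecting a preoperative QLQ-C30 that enters no stated comparison. The planned tests are valid, and no design target is missed.

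The size of the loss cannot be taken from the documents. For the primary outcome it is about 2.5 to 6.5 points of power at 64 per arm if R² is 0.10 to 0.30, and nothing if the factors turn out not to be prognostic. For QLQ-C30 the available variance reduction may be larger, 9% to 51% against the 1-month score, but this concerns a secondary outcome. Because the remedy is nearly free while the data are unanalysed, it is worth making.

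**What to change.** Before database lock:

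1. Pre-specify a regression for time to first flatus, adjusted for a short fixed list of factors that acupuncture cannot affect: operation type or tumour site, and tumour stage. Acupuncture starts the day after surgery, so both are settled before it can act. Report the unadjusted test alongside.
2. Analyse 1-month QLQ-C30 by ANCOVA on the preoperative score, and postoperative laboratory values on the preoperative value.
3. Reconcile section {20a} with the mixed-model remark in {20c}: either define the model, its outcomes and its covariates, or delete the remark.
4. Do not use rectal-tube presence as a covariate or an exclusion in the primary analysis. At most, record presence and time of insertion, and run a sensitivity analysis only if insertion preceded randomisation.

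The cost is some analysis-plan wording, a little extra analysis work, and the discipline of fixing the covariate list in advance. Randomisation and enrolment do not change; with recruitment reported as ongoing, adjustment is more practical than introducing stratification.
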